#### Topics

In the first meeting participants are encouraged to think about the influence arthritis has on their lives. Four narratives of fictive patients are introduced that are used throughout the whole program to discuss adaptation and the use of goal management strategies. Themes presented in the narratives are threatened personal goals, the goal management strategies, the role of the social environment, and accompanying emotions. Central in the first meeting is recognition, accomplished through comparison of the participant’s own situation with the aforementioned narratives and through the exchange of experiences with other participants. Topics in the second meeting are identifying threatened personal goals and becoming acquainted with the various goal management strategies. Participants are encouraged to explore attitudes, behaviors and emotions related to the goal management strategies, using figures that depict the various strategies (Figure 1).

**Figure 1 F1:**
[figure not shown]
**Illustratons that depict the four goal management strategies (A-D)**^**#**^**. **^#^ Copyright: 2012 [name], [name], [name], [name].

By formulating lower and higher order goals and discussing the goal management strategies, participants gain insights into their own behavior and preferences for strategies regarding vital threatened goals. In addition, by using the goal hierarchy pyramid (see Figure 2) to differentiate between higher order and lower order goals, participants will be helped to choose suitable goal management strategies for threatened goals at a later stage.

**Figure 2 F2:**
[figure not shown]
**Example of the Goal hierarchy pyramid**^**#**^**. **^#^Note. *Instructions:* Choose an activity that you care about and that is threatened by your rheumatic condition. Write the activity on the bottom layer of the pyramid. Consider whether there is a ‘higher’ goal you can put on the level above. It may help to ask yourself the following questions: Why is this important for me? What is it about the activity that appeals to me? Not all levels in the pyramid always need to be filled, just try to work your way up the pyramid as far as you can.

During the next meetings, participants choose a threatened activity and a suitable goal management strategy, and formulate and execute a personal action plan for the activity (meetings 3, 4 and 5). Every step in this process is evaluated individually by homework exercises and discussed in a group setting. In the fourth meeting, resistance to change and support from the social environment are also addressed. Central in the fifth and sixth meetings is the execution of alternative goal management strategies. In the sixth meeting, the consolidation of learned skills and competencies and the prevention of relapse in unbeneficial behavior are also addressed. Personal warning signs are used to anticipate a relapse into undesired behavior and also the use of support from the social environment is stimulated to prevent relapse.

#### Behavior change techniques

Many health psychologists have argued for a more precise description of intervention content, including specifying techniques used to accomplish behavior change [61]. The explicit communication of intervention content is necessary to study effective ingredients and to further improve the effectiveness of interventions in the future. In the context of these developments, the techniques used in the program are listed for each meeting in Table 2. A couple of techniques that originated from cognitive behavior therapy are used to stimulate the flexible use of the goal management strategies. Those techniques are used regularly in psychosocial interventions: group discussions, personal feedback, planning, self-examination and mental simulation (see Table 2 for a complete list). In particular, the technique of mental simulation is used to stimulate people to apply a new, and until now not preferred, goal management strategy. Progress to achieve goals is reached through the mental simulation of the initiation and maintenance of activities that help to reach a goal [64]. This technique has shown its feasibility and effectiveness in other studies [65,66].

#### Trainers

Specialized nurses in rheumatology care train and support the groups. Participants have the same trainer during the entire intervention period. Before the start of the program, the nurses received a full day ‘train-the-trainer’ course. In this training, the nurses worked through the entire program as a participant and completed the homework assignments to experience the techniques used in the program. In a second phase, the nurses gave the exercises themselves and received detailed feedback on their performance. At the end of the train-the-trainer course, trainers’ knowledge and skills concerning goal management and learned intervention techniques were evaluated. During the study period, trainers receive monitoring and regular supervision by a psychologist.

### Control condition

Participants in the waiting list condition do not receive the “Right On Target” program immediately. Eight months after entry into the study, which is directly after the last follow-up measurement, participants on the waiting list are invited to follow the program.

### Measurements

Table 3 gives an overview of the properties of the measurement instruments used. Participants are asked to complete six questionnaires including: intake, baseline (T0), directly after the end of the program (T1), 2 months after the end of the program (T2), 4 months after the end of the program (T3), and 6 months after the end of the program (T4). Nearly all the instruments listed in Table 3 were applied in a previous study with polyarthritis patients [12], and, when available, Cronbach’s alphas from that previous study also appear in Table 3.

**Table 3 T3:** Study parameters, properties of the corresponding instruments and their measurement point(s)

**Content**	**Measurement point**	**Scale**	**Reference**	**Example item**	**Scale range**	**Cronbach’s alpha **^**a**^	**Items**	**Response options**
Depression	Intake, T0, T1, T4	Hospital Anxiety and Depression Scale (HADS)	Zigmond & Snaith, 1983 [60]	I have lost interest in my appearance.	0-21	.81	7	various response format (0–3)
Anxiety	Intake, T0, T1, T4	HADS	Zigmond & Snaith, 1983	I feel tense or wound up.	0-21	.83	7	various response format (0–3)
Positive affect	T0, T1, T4	Positive subscale of the Positive and Negative Affect Schedule (PANAS)	Watson, Clark, & Tellegen, 1988 [67]	Rate how you felt during the past week: e.g., *attentive*, *interested*.	10-50	.92	10	very slightly or not at all (1) - very much (5)
Purpose in life	T0, T1, T4	Purpose In Life scale (PIL)	Ryff, 1989 [68]; Ryff & Keyes, 1995 [69]	My daily activities often seem trivial and unimportant to me.	6-30	.82	6	strongly disagree (1) -strongly agree (5)
Social participation	T0, T1, T4	Family role, autonomy outdoors, social relations and work and education subscales of the Impact on Participation and Autonomy (IPA) questionnaire	Cardol, De Haan, De Jong, Van den Bos, & De Groot, 2001 [70]	Domain autonomy outdoors: The possibility to spend my (spare) time like I want to is…	0-4	.76	25	very good (0) - very poor (4)
Pain	T0, T1, T4	1 item with 100 mm visual analogue scale	-	Please indicate how much pain you had in the last 7 days due to your condition?	0-100	-	1	no pain at all (0) -unbearable pain (100)
Fatigue	T0, T1, T4	1 item with 100 mm visual analogue scale	-	Please indicate your level of fatigue averaged over the past 7 days?	0-100	-	1	no fatigue (0) -completely exhausted (100)
Physical functioning	T0, T1, T4	RAND-36 physical function subscale	Ware & Sherbourne, 1992 [71]; Van der Zee & Sanderman, 2012 [72]	Does your health limit you in these activities? If so, how much? E.g., Walking a half mile.	10-30	-	10	Yes, limited a lot (1) – No, not limited at all (3)
Goal maintenance	T0, T1, T4	Tenacious Goal Pursuit (TGP)	Brandtstädter & Renner, 1990 [73]	When faced with difficulties, I usually double my efforts.	15-75	.73	15	strongly disagree (1) -strongly agree (5)
Goal adjustment	T0, T1, T4	Flexible Goal Adjustment Scale (FGA)	Brandtstädter & Renner, 1990	I adapt quite easily to changes in plans or circumstances.	15-75	.79	15	strongly disagree (1) -strongly agree (5)
Goal disengagement	T0, T1, T4	Goal Adjustment Scale	Wrosch, Scheier, Miller, et al., 2003 [42]	If I have to stop pursuing an important goal in my life, *it’s easy for me to reduce my effort towards a goal.*	4-20	.53	4	strongly disagree (1) -strongly agree (5)
Goal reengagement	T0, T1, T4	Goal Adjustment Scale	Wrosch, Scheier, Miller, et al., 2003	If I have to stop pursuing an important goal in my life, *I seek other meaningful goals.*	6-30	.88	6	strongly disagree (1) -strongly agree (5)
Goal management strategies	T0, T1, T4	Goal Management Strategy Vignettes (GMSV)		See article’s text	-	-	-	Open ended
Coping versatility	T0, T1, T4	Coping Flexibility Questionnaire (COFLEX)	Vriezekolk, Van Lankveld, Eijsbouts, Van Helmond, Geenen, & Van den Ende, 2012 [51]	I can easily change my approach if necessary.	9-36	-	9	rarely or never (1) –almost always (4)
Self-efficacy pain	T0, T1, T4	Arthritis Self-Efficacy Scale	Lorig, et al., 1989 [30]	I am certain that I can keep arthritis pain from interfering with my sleep.	1-5	.83	5	strongly disagree (1) -strongly agree (5)
Self-efficacy for other symptoms	T0, T1, T4	Arthritis Self-Efficacy Scale	Lorig, et al., 1989	I am certain that I can control my fatigue.	1-5	.82	6	strongly disagree (1) -strongly agree (5)
Demographics	T0	Sex, age, marital status, education and current state of employment	-	-	-	N.A.	6	various response format
Disease characteristics	T0	Diagnosis and disease duration	-	-	-	N.A.	2	Various response format
Co-morbidities	T0	Checklist with 15 categories of conditions ^b^	Based on the International Classification of Diseases (ICD-10: WHO, 1992)	-	0-16	N.A.	16	-
Medication use	T0, T1, T2, T3, T4	-	-	See article’s text	N.A.	N.A.	2	See text
Utilities	T0, T1, T4	EQ-5D	Brooks, 1996 [74]; Lamers, McDonnell, Stalmeier, Krabbe, & Busschbach, 2006 [75]	I have no problems in walking about.	1-3	-	15	No problem (1) - extreme problems (3)
Direct medical costs	T0, T1, T2, T3, T4	-	-	See article’s text	N.A.	N.A.	3	Open ended
Indirect non-medical costs	T0, T1, T2, T3, T4	-	-	See article’s text	N.A.	N.A.	7	Open ended
Price estimate	T1	-	-	See article’s text	N.A.	N.A.	1	In euros for de complete course

^a^ Arends et al., 2013; ^b^ Respondents could also indicate ‘*other conditions not listed*’.

### Primary outcome measure

#### Depressive symptoms

The *depression* subscale of the Hospital Anxiety and Depression Scale (HADS) [60] is used. The HADS was chosen because the scale is designed to measure the presence and severity of depressive and anxiety symptoms whilst limiting any confounding effects of physical illness symptoms by excluding somatic items. The HADS is used both in earlier studies with arthritis patients (e.g., [54] and in studies on goal management [57]), which facilitates comparison of study results. The HADS is also used in other interventions intended to influence depressive symptoms [76]. Concurrent validity of the HADS is very satisfactory and the measure has sufficient internal consistencies [59,60].

### Secondary outcome measures

#### Anxiety

The *anxiety* subscale of the HADS [60] is used to measure anxiety symptoms.

#### Positive affect

The *positive* subscale of the Positive and Negative Affect Schedule (PANAS) [67] is used for the measurement of positive affect.

#### Purpose in life

To assess the extent wherein participants experience a meaningful life, the Purpose In Life Scale (PIL) [68,69] is used. This scale is comprised of 5 items about a person’s experience with respect to the presence or absence of life goals. One question about everyday purpose in life is added to the PIL: ‘*Doing the things I do everyday is a source of deep pleasure and satisfaction*’.

#### Participation

The Impact on Participation and Autonomy (IPA) [70] questionnaire assesses the participants’ satisfaction with social participation. We use the subscales *family role*, *autonomy outdoors*, *social relations*, and *work and education* to quantify impediments in participation and autonomy.

#### Pain

The severity of pain in the past week is measured by a 1-item visual analogue scale.

#### Fatigue

The severity of fatigue in the past week is measured by a 1-item visual analogue scale.

#### Physical functioning

The physical functioning subscale of the RAND-36 [71,72,77] is selected to measure physical functioning.

### Measures of mediation variables

To measure the use of goal management strategies, we use three generic disease questionnaires, and one disease-specific instrument especially designed to measure goal management in arthritis patients.

#### Maintenance of goals and adjustment of goals

The tendencies to use the strategies maintaining goals and adjusting goals are measured by the Tenacious Goal Pursuit and Flexible Goal Adjustment scales (FLEXTEN: TGP & FGA subscales) [73].

#### Goal disengagement and goal reengagement

The tendencies to use the strategies goal disengagement and goal reengagement are measured with the Goal Adjustment Scale (GAS) [42].

#### Goal management strategy vignettes

We have developed vignettes for explorative purposes in this program called Goal Management Strategy Vignettes (GMSV). Three vignettes are used to measure the extent in which a person is flexible in thinking about goal management. The vignettes are short stories of a person with arthritis who struggles with threatened personal goals in the domains of social relationships, leisure time and autonomy. To respond, the participant writes down possible ways in which the vignette character can react to the situation described. To analyze the answers, deductive coding for similarity with pre-defined strategies is used. To measure flexibility in thinking of goal management, the increase in the number of strategies that are mentioned per time point is used.

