### Randomization

The participants are assigned in a 1:1 ratio to either the experimental group or the control group. Patient allocation is be done by means of blocked stratified randomisation per site in random block sizes of 2 and 4 to make sure that both conditions are equally distributed in each participating hospital. The study is open label, as it is impossible, due to the nature of the program, to blind the staff and participants involved to the condition which the patient is allocated.

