### Experimental condition

The program consists of six group-based meetings with 8 to 10 participants and individual homework assignments. “Doelbewust!” is a protocol-based psychosocial educational program. *Doelbewust* is the Dutch word for “purposefully” and we have translated this program name into English as “Right On Target”. The program is led by a trained nurse. Participants are introduced to different goal management strategies and learn to use these strategies to cope in a flexible way with threatened personal goals. The goal management strategies that are covered in the program are: goal maintenance, goal adjustment, goal disengagement, and goal reengagement [39-42].

Table 2 lists the topics, goals, and applied techniques for each meeting of the program. The general structure of each meeting is as follows: a short review of the contents of the previous meeting; introducing the topics of the current meeting; elaborating the topics by group discussions and by practicing in individual, dual and group exercises; and explaining homework assignments for the next meeting. A pilot was executed to test the feasibility of the program protocol.

**Table 2 T2:** Contents of the goal management program

**Meeting**	**Topic**	**Main goals meeting**	**Applied techniques**^**#**^
1.	Arthritis in daily life	Become aware of the influence of polyarthritis in the different domains of life.	Information (general), instruction, problem identification, behavioral information (narratives), modeling (by narratives), vicarious reinforcement (narratives), comparison (with narratives and other participants), emotional social support (by other participants), set homework tasks, prompt (email after meeting to do homework).

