#### Analysis of mediation

Multiple mediation analysis will be performed to analyze whether the tendencies to use goal management strategies and coping versatility mediate the effects in the intervention. Primary and secondary outcomes used are the measures of depression, anxiety, purpose in life, positive affect and participation. Baseline and post-intervention measurements of both intervention and waiting list group will be used. A change score for tendencies to use goal management strategies and coping versatility will be computed with scores from baseline and post-intervention measurement. Multiple mediation analysis with bootstrapping procedures (n = 5000 bootstrap re-samples) will be used to assess the indirect effect of the mediation pattern, as recommended by Preacher and Hayes [80]. An indirect effect will be considered significant in the case when zero is not contained in the 95% bias-corrected confidence interval. Self-efficacy pain and self-efficacy for other symptoms will be incorporated in the multiple mediation analyzes as putative mediators. To analyze whether the GSMV mediate the effects of the intervention on the primary and secondary outcome measures, dummy variables will be used to indicate whether or not a strategy is named.

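### The general statement that staff cannot be blinded makes no exception for coding the free-text vignettes, the one rater-judged measure, where masked coding would be feasible and cheap (minor)

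*Protocol article*

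**What the plan says.** On blinding, the Randomization section states: "The study is open label, as it is impossible, due to the nature of the program, to blind the staff and participants involved". It makes no exception for any later task.

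On the vignettes, the section Goal management strategy vignettes says that "the participant writes down possible ways in which the vignette character can react to the situation described". There are three vignettes, and Table 3 lists the response as open ended at T0, T1 and T4. The scoring is described in one sentence: "To analyze the answers, deductive coding for similarity with pre-defined strategies is used". For flexibility in thinking about goal management, "the increase in the number of strategies that are mentioned per time point is used". The same section introduces the instrument with this status: "We have developed vignettes for explorative purposes in this program".

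On use, the section Analysis of mediation asks whether the vignettes mediate the effect on the primary and secondary outcomes, and says that "dummy variables will be used to indicate whether or not a strategy is named".

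On content, the section Experimental condition states: "The goal management strategies that are covered in the program are: goal maintenance, goal adjustment, goal disengagement, and goal reengagement".

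**The concern.** The reason given for the open-label design applies to people who attend or lead meetings. It does not apply to someone who reads written answers afterwards, who need not know the arm.

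The task calls for judgement, namely whether a free-text answer resembles a given strategy. Those strategies are very probably the ones that only the programme arm has been taught before T4. A coder who knows that an answer comes from a programme participant at T1 or T4 would expect to find them, and in doubtful cases may credit them more readily. Such an error would arise in one arm and only after T0, so subtracting the baseline count would not remove it.

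At stake are the exploratory flexibility score and the vignette part of the mediation analysis.

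**Working it through.** **1. Does the stated reason cover the coding?** The Randomization section rests on the nature of the programme. The vignette section describes a written response that is coded later. Nothing about the programme obliges the coder to know the arm. The statement is therefore wider than its reason.

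**2. Is this the only exposed measure?** By Table 3 and the measurement sections:
- The primary and secondary outcomes are self-completed scales with fixed responses or visual analogue scales.
- The other mediators (tenacious goal pursuit, flexible goal adjustment, goal disengagement and reengagement, coping versatility, self-efficacy) are fixed-response scales.
- The other open-ended items (medication, costs) ask for facts or counts.
- Only the vignettes are scored by judging what an answer means.

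**3. Are the coded strategies those taught?** The vignette section does not list its pre-defined strategies. The article describes one set of four throughout, and the programme teaches those four. Identity is almost certain but is an inference.

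**4. What do the documents say about the coder?** They do not say who codes, or whether arm or time point is masked.

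**5. Where would a bias go?**
- The flexibility score is the increase in strategies mentioned, so over-crediting at T1 or T4 in one arm passes straight into it.
- The mediation section uses baseline and post-intervention data, so the T1 codes are the post-baseline ones that matter there.
- The indirect effect is a × b, where a is the arm-to-mediator path and b the mediator-to-outcome path. Suppose a share p of both arms truly names a strategy, and a coder wrongly credits it in a share f of the programme answers that lack it. Then the apparent a is (p + (1 − p)f) − p = (1 − p)f, although the true a is zero.
- The apparent indirect effect is (1 − p)f × b. It is zero if b is zero. Over-crediting unrelated to outcome does not create b, and tends to weaken it.

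**6. Can a size be given?** Not from the documents, because p and f appear nowhere in them. The table only illustrates the first path. It assumes 100 per arm (the figure in the Sample size section), no true difference, and a two-sided 5% comparison of two proportions. The last column is the chance of a false significant result favouring the programme; nominal is 2.5%.

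| assumed p | assumed f | false difference (1 − p)f | chance |
|---|---|---|---|
| 0.30 | 0.05 | 0.70 × 0.05 = 3.5 points | 7.6% |
| 0.30 | 0.10 | 0.70 × 0.10 = 7.0 points | 18.0% |
| 0.30 | 0.20 | 0.70 × 0.20 = 14.0 points | 53.6% |
| 0.50 | 0.05 | 0.50 × 0.05 = 2.5 points | 5.4% |
| 0.50 | 0.10 | 0.50 × 0.10 = 5.0 points | 10.5% |
| 0.50 | 0.20 | 0.50 × 0.20 = 10.0 points | 29.4% |

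This is not the planned test, which bootstraps the indirect effect. The table shows only that the result depends heavily on an unknown error rate.

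**The case against.** The strongest reply is that the article never says coding is unmasked. A reader might infer that study staff who know the allocation will code the answers. The documents do not support that: no coder is named, and the staff who are said to be impossible to blind can be read as those who deliver the programme. A condensed article may also leave coder masking to a fuller document that is not shown. This part of the objection stands, and silence about the coder alone would not be a finding. What remains is narrower. The article makes a general statement about staff, gives a reason that does not reach this task, and names no exception. Followed as written, it leaves the coding unprotected.

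The second reply concerns the stakes. The vignettes are labelled explorative, the main mediators are self-report scales, and the Discussion says that the additional analyses cannot be conducted if there is no effect against the waiting list. This also stands. A reader might infer that coder bias threatens the main result or could by itself produce a mediation finding. It could do neither. The depression subscale involves no rater, and a false indirect effect also needs a mediator-to-outcome relation.

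Third, course terms in programme answers may reveal the arm, so masking cannot be complete. That limits the benefit but does not argue for leaving arm and time point visible.

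**Conclusion.** The point holds as a minor one. The open-label statement is broader than its own justification, and it leaves the single rater-judged measure without stated protection against coder expectation. The consequence is confined to the exploratory flexibility score and to the arm-to-mediator path in the vignette mediation analysis. The primary analysis of depressive symptoms and the sample size are unaffected.

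The conclusion rests on two assumptions: that the pre-defined strategies are the four taught in the programme, and that no masking of coders is laid down elsewhere. No magnitude should be attached to the bias, since the documents contain no coding-error rate.

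**What to change.** In Randomization, limit the statement that blinding is impossible to participants and those who deliver the programme.

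In Goal management strategy vignettes, state that:
- the T0, T1 and T4 answers from both arms are de-identified and filed under a random number;
- they are mixed in random order and coded without arm or time point;
- the codes are locked before the allocation is merged.

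The answers have to be coded in any case, so the added cost is the de-identifying and shuffling, plus transcription if the answers are handwritten. Masking will be partial where course vocabulary shows through. Excluding trainers and their supervisors as coders would be a further safeguard, but it may need extra staff and is not a condition of this fix.
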